### Study procedures and informed consent

Procedures for the validation study involve a one-time research visit. All participants will complete the TAPS-ESP in both interviewer- and self-administered formats. However, to test for administration order effects, the order of the format will be determined at random, see Fig. 1 for SPIRIT flow diagram. Randomization addresses confounding by administration order, thereby allowing an unbiased comparison of self- and interviewer-administration formats (both of which are widely used in clinical care). This design was used in the original TAPS study and our prior work [42]. Randomization is automated, with minimal extra time burden.

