#### Comparisons by administration format, sex, and age

We will conduct all analyses separately for (a) the interviewer-administered TAPS-ESP, and (b) the self-administered TAPS-ESP. In addition, we exploit the random-order design to directly compare the administration formats in their ability to elicit self-disclosure of substance use, and in their performance with respect to sensitivity, specificity, and ROC curves. We anticipate a fairly balanced representation of male and female participants, as well as adults across the lifespan, and thus will also examine TAPS-ESP performance based on participant sex and age. We will employ a combination of subgroup analyses and multivariable logistic regression models to comprehensively examine these factors. This approach replicates the rigorous analysis strategy of the English language TAPS study [16, 18, 35].

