### Power

Our power analysis used the approach for minimum sample size determination for sensitivity and specificity analyses as recommended by Bujang and Adnan [56]. These authors computed minimal sample size requirements for screening and diagnostic validation studies under a range of scenarios regarding the prevalence of the disease in the clinical population. Although substance use problems as a whole are prevalent in primary care populations, prevalence is expected to be low for specific SUDs. For a screening study, particularly one with a low prevalence of disease, achieving high sensitivity (i.e., the ability of the test to accurately detect a true case of the condition; true positives) is paramount, and much lower sample sizes are needed for specificity. Thus, we present power calculations for sensitivity as recommended for screening studies, where the prevalence of the disease/condition is low, ranging from 2.5–20%, where power > 0.80 and the null hypothesis is 0.50. Our target sample size of *N* = 1000 exceeds the maximum sample size requirements for screening studies even at a low prevalence of 5%, even if the screening performs only in the “acceptable” range (Table 2). If, as expected, the TAPS-ESP performs in the “good” or “excellent” range (with sensitivities exceeding 0.80 or 0.90), a smaller sample size would be sufficient, even at very low prevalence of 2.5%. The approach detailed above is recommended for screening studies against a diagnostic standard. Nonetheless, we also computed power to detect differences in sensitivity between the TAPS-ESP and other screeners, using the Stata/SE 16 PSS command suite for differences in marginal proportions in dependent samples. We assumed high within-subject correlations and base sensitivity of 0.70 in the comparison screener. At 10% prevalence, power to detect a 10% improvement in sensitivity approached 0.90, but fell below 0.70 when prevalence was set at 5%. Power remained good (0.80) at prevalence of 5% to detect a slightly larger improvement in sensitivity of 15%.

**Table 2 Tab2:** Minimum sample size for sensitivity in screening studies, with power > 0.80, α = 0.05, and H_0_ = 0.50

Prevalence	H_1_	N_positive_	N_Total_
2.5%	0.70	49	1960
2.5%	0.80	20	800
5%	0.70	49	**980**
5%	0.80	20	400
10%	0.70	49	490
10%	0.80	20	200
20%	0.70	49	245
20%	0.80	20	100

The bolded value of 980 formed the basis for our sample size determination, assuming 5% prevalence

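### Random order removes the average period effect only; a format comparison that uses second administrations is unbiased only if carryover is absent or equal and additive

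*Protocol article*

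**What the plan says.** Under Study procedures and informed consent, the protocol article states: "Procedures for the validation study involve a one-time research visit". It continues: "All participants will complete the TAPS-ESP in both interviewer- and self-administered formats". The stated purpose of randomising is "to test for administration order effects, the order of the format will be determined at random". The article then infers: "Randomization addresses confounding by administration order, thereby allowing an unbiased comparison of self- and interviewer-administration formats".

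Under Comparisons by administration format, sex, and age, the analysis is described in two parts. First: "We will conduct all analyses separately for (a) the interviewer-administered TAPS-ESP, and (b) the self-administered TAPS-ESP". Second, "we exploit the random-order design to directly compare the administration formats in their ability to elicit self-disclosure of substance use"; the same sentence extends the comparison to sensitivity, specificity and ROC curves.

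The article does not say whether the format comparison uses first administrations only, both administrations, or each in turn. It states no interval between the two administrations and does not mention carryover, recall or consistency of answers.

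**The concern.** This is a two-period, two-sequence design without a stated washout, and the instrument is the same in both periods. Random order ensures that neither format sits more often in the second position, so an average shift between first and second administration cancels. Carryover is a different matter. A participant who has just told an interviewer that they do not use a substance has reason to give the same answer on the tablet minutes later, and the reverse can also happen. Randomising the order spreads that influence over both formats; it does not remove it.

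What is at stake is the comparison for which the random order is said to be exploited: whether one format elicits more disclosure. If answers are repeated, a pooled analysis moves towards finding the formats alike, and the word unbiased in the procedures section would then be available to defend that finding. The per-format accuracy estimates are touched too. About half the responses in each format are second administrations, whereas a patient screened once in clinic gives only a first administration.

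**Working it through.** **The plan's own figure.** Table 2 is headed "Minimum sample size for sensitivity in screening studies, with power > 0.80, α = 0.05, and H_0_ = 0.50", and "The bolded value of 980 formed the basis for our sample size determination, assuming 5% prevalence". With an exact two-sided binomial test and 49 positives, the test rejects at 32 or more; the type I error is 0.044 and power at 0.70 is 0.810. Then 49 / 0.05 = 980. With 20 positives it rejects at 15 or more, with power 0.804 at 0.80, and 20 / 0.05 = 400. Table 2 is sound for its own purpose. No sample size, power or effect size is given for the format comparison.

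If the 49 positives are meant to apply to each format, they need every participant's response in that format. First administrations alone give about 1000 × 0.05 / 2 = 25 positives per format, and the same exact test then has power 0.51.

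**Inputs from the article.** Two administrations per participant, one visit, order assigned at random, N = 1000, 5% prevalence.

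**Assumptions, not in the article.** Order is split 1:1. First-administration sensitivity is S = 0.80 (self) and I = 0.70 (interviewer), a true difference of 0.10. A share c of second answers repeats the first.

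**Repeated answers.**
- Self-first: self = S; interviewer = cS + (1 − c)I.
- Interviewer-first: interviewer = I; self = cI + (1 − c)S.
- Average over the two orders: self − interviewer = (1 − c)(S − I).
- First administrations only: S − I, whatever c is.
- Second administrations only: (1 − 2c)(S − I).

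| c | First only | Second only | Pooled |
|---|---|---|---|
| 0 | 0.100 | 0.100 | 0.100 |
| 0.25 | 0.100 | 0.050 | 0.075 |
| 0.50 | 0.100 | 0.000 | 0.050 |
| 0.75 | 0.100 | −0.050 | 0.025 |
| 0.90 | 0.100 | −0.080 | 0.010 |
| 1 | 0.100 | −0.100 | 0.000 |

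A simulation of 2,000,000 participants gave pooled differences of 0.100, 0.050 and 0.010 at c = 0, 0.5 and 0.9, and a first-administration difference of 0.100 throughout.

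**Additive carryover.** Let the interviewer format add k1 to a following self answer, and the self format add k2 to a following interviewer answer. The pooled difference is (S − I) + (k1 − k2)/2.
- k1 = k2 = 0.05: 0.100, no bias.
- k1 = 0.05, k2 = 0: 0.125, inflated.
- k1 = 0, k2 = 0.05: 0.075, shrunk.

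**Precision for disclosure** (80% power, two-sided 5%, p = average disclosure rate, an assumption).
- First administrations, 500 per order: 2.8 × √(2p(1 − p)/500) = 0.053 at p = 0.10 and 0.071 at p = 0.20.
- Paired, N = 1000, within-person correlation 0.8 (an assumption): 2.8 × √(2p(1 − p)(1 − 0.8)/1000) = 0.017 and 0.022.

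**Precision for sensitivity** (0.80 v 0.70, first administrations). Power is about 0.13 with 25 cases per order, 0.21 with 50 and 0.37 with 100. About 294 cases per order are needed for 80%.

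**The case against.** Four objections deserve weight.

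1. *The sentence can be read correctly.* It says randomisation allows an unbiased comparison, and it does allow one: self-first against interviewer-first. This stands, and it rules out the stronger reading that randomised order permits no unbiased format comparison. What remains is that the article does not tie the claim to that contrast, while its design and per-format analyses take in second administrations.

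2. *The article does not commit to pooling, and such detail may sit in an analysis plan that is not shown.* This also stands, so silence on the model is not the point. The point is the stated inference from random order to lack of bias, which is too broad for any analysis that uses second administrations.

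3. *A test of order effects is already planned.* True, but it does not make a pooled estimate unbiased, and depending on its form it may miss repeated answers. In the example at c = 0.5, the self-first group has 0.80 and 0.75 and the interviewer-first group has 0.70 and 0.75. The mean is 0.75 in both positions, and the self − interviewer difference is 0.05 in both orders. Neither contrast reveals the halving.

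4. *Carryover, its size and its direction are not documented.* This stands. A reader might infer that carryover is present, that it must shrink the difference, or that a finding of similar formats would be an artefact. The article has no data to support any of these; equal additive carryover leaves no bias, and unequal carryover can inflate the difference.

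It is also fair to say that replacing the paired comparison with the first-administration one would be a trade of variance for bias. The sensitivity figures show how steep that trade is.

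**Conclusion.** The claim is too broad as written. Random order deals with the average period effect; for analyses that use second administrations, lack of bias needs the further condition that carryover is absent or equal and additive. The article states no such condition, and identical items at one visit make it doubtful. Under repeated answers the pooled difference is (1 − c) of the truth, so the loss ranges from nothing at c = 0 to all of it at c = 1; c, the 10-point difference and the additive values are illustrations only.

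Severity is moderate. A reader might infer that the validation itself or the sample size is undermined. The documents do not support that: the primary outcome is detection of SUD against the CIDI, Table 2 reproduces, and first-administration results in either format are untouched. Only the format comparison and the second-administration share of the per-format estimates are exposed.

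**What to change.** - **Study procedures and informed consent.** Either say that random order balances period effects, or tie the word unbiased to the comparison of self-first with interviewer-first participants.
- **Comparisons by administration format, sex, and age.** Add that between-group comparison for disclosure as the carryover-free analysis. Report each format's sensitivity and specificity on first administrations alongside all administrations.
- **Paired comparison.** Keep it, with clustering on participant (for example GEE) and terms for format, order and format-by-order. Code order as position, first or second. The interaction then contrasts the format difference at first administration with that at second: 2c(S − I) under repeated answers. Coded as sequence, the interaction would be zero in that case. It is a between-person contrast, so a non-significant result does not show that carryover is absent.
- **State the downside.** With about 500 per order, the detectable disclosure difference is about 5 to 7 points at 10% to 20% disclosure. At 5% prevalence, first-administration sensitivity rests on about 25 cases per order, with power about 0.13 for 0.80 v 0.70, so those comparisons should be presented as estimates with intervals.

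The cost is wording and some added analysis. Order is assigned by an automated randomisation, so no new data, participants or visits are needed.

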**Fig. 1 Fig1:**
[figure not shown]
Recruitment and procedures flow for the validation study

After completing the TAPS-ESP in both formats, participants will complete a battery of self-report measures for validation purposes, as well as a brief satisfaction and acceptability questionnaire. Self-report measures will be interviewer administered only. Participants will receive $40 for completing the self-report portion of the validation study, which is expected to take about 1.5–2.0 h for participants who report polysubstance use. Because this is a validation study, participants will be informed at the outset that each measure must be asked in its entirety, and to expect some redundancy in the questions. Nevertheless, the assessment may be slightly shorter in duration for participants with limited substance use due to skip patterns that exist within each measure.

At the conclusion of the self-report measures, participants will be invited to provide an oral fluid cheek swab, which will undergo rapid assay testing for biomarkers of recent substance use. Participants will be asked to sign a separate consent for the oral fluid testing and will receive an extra $10 for providing a sample. This approach will be undertaken to ensure that self-report measures are assessed free of bias that may occur if participants know ahead of time that they will be tested. This will serve as a test of the veracity of the self-report information obtained from participants. We will track refusal to consent to the oral fluid test component and will analyze these data under different assumptions (e.g., completers only; refusals imputed as positive). Participants will also be asked about medications they are taking as prescribed in order to account for medicines that may be reactive with the tests.

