#### Primary criterion standard for validation

*Modified World Mental Health Composite International Diagnostic Interview (CIDI):* The CIDI is a comprehensive instrument used to assess mental health disorders based on criteria in the International Classification of Diseases (ICD-10) and the Diagnostic and Statistical Manual of Mental Disorders (DSM-IV and DSM-5). Substances covered in the CIDI are alcohol, tobacco, and nine substance categories. As is the methodological standard in the field and as done in our prior research [42], we will administer a modified version of the CIDI consisting of the subset of items mapping to DSM-5 substance use disorder (SUD) criteria, asked for each endorsed substance class. We will examine categories of unhealthy use (1 DSM criterion) and SUD (2 + criteria), using the CIDI as the “gold standard” for identifying SUDs (i.e., patients at higher risk) [47, 48]. This is consistent with the methodology of the original English-language TAPS study and many other validation studies. The CIDI items mapped to the DSM-5 criteria for each substance will serve as the primary criterion standard.

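### Random format order does not make the CIDI-referenced comparison of TAPS-ESP formats unbiased, because the CIDI shares its interview mode with only one of the two formats

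*Protocol article*

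**What the plan says.** Four parts of the protocol article bear on this.

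- **Design.** *Study procedures and informed consent*: "All participants will complete the TAPS-ESP in both interviewer- and self-administered formats". Only the order of the formats is random, and the article draws this conclusion: "Randomization addresses confounding by administration order, thereby allowing an unbiased comparison of self- and interviewer-administration formats".
- **What is compared.** *Comparisons by administration format, sex, and age* lists two things. One is how well each format elicits self-disclosure. The other is how the formats differ "in their performance with respect to sensitivity, specificity, and ROC curves".
- **The reference.** *Primary criterion standard for validation*: "The CIDI items mapped to the DSM-5 criteria for each substance will serve as the primary criterion standard". The items are "asked for each endorsed substance class".
- **How the reference is obtained.** In the procedures text after Fig. 1: "After completing the TAPS-ESP in both formats, participants will complete a battery of self-report measures for validation purposes", and then: "Self-report measures will be interviewer administered only".

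The article also plans an oral fluid assay as an objective check on self-report. It notes that the assay captures recent use only and that participants consent to it separately.

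**The concern.** Self-disclosure can be compared between formats without a reference. Sensitivity, specificity and ROC curves cannot. Their reference is itself an interview, so any tendency to deny use to an interviewer affects the interviewer-administered TAPS-ESP and the CIDI together. It need not affect the tablet in the same way.

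Take a participant with a disorder who denies use to interviewers but reports it on the tablet. The CIDI criteria are asked per endorsed class, so the denial leaves the reference negative. The interviewer format then scores a true negative and the self format a false positive, although the tablet gave the right answer.

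Randomising which format comes first balances practice, fatigue and carry-over between the formats. It does nothing about error in a reference that comes after both formats and matches the mode of one. The plan treats disclosure as possibly depending on mode, since it compares the formats on exactly that. If mode can change answers on the TAPS-ESP, it can change answers on the CIDI.

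The article says that both formats are in wide clinical use. A between-format difference in accuracy reported as unbiased could therefore be read as a reason to prefer one.

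**Working it through.** **The plan's own figure.** The plan gives no figure for this bias. Its sample size is unaffected: Table 2 needs 49 positives for sensitivity 0.70 against 0.50. An exact two-sided 5% test with n = 49 rejects at 32 or more and has power 0.810, and 49 / 0.05 = 980, as stated.

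**Inputs from the article.** Both formats in every participant; random order; CIDI by interviewer only, after both formats; CIDI items asked per endorsed class.

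**Inputs not in the article (assumed).** A share d = 0.80 of true cases discloses in each mode, including to the CIDI. Each format detects 90% of those who disclose in it. CIDI-positive means disclosed to the CIDI interviewer. Disclosure in two settings follows a bivariate normal model with correlation r.

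**Formula.** Measured sensitivity = 0.9 × P(disclose in the format | disclose to the CIDI). True sensitivity is 0.9 × 0.80 = 0.72 for both formats, so the true difference is 0.

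| r between format and CIDI disclosure | P(disclose in format given disclosed to CIDI) | Measured sensitivity |
|---|---|---|
| 0 | 0.800 | 0.720 |
| 0.5 | 0.859 | 0.773 |
| 0.8 | 0.911 | 0.820 |
| 0.9 | 0.937 | 0.844 |
| 1 (identical) | 1.000 | 0.900 |

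The spurious self-format deficit is the difference between two rows:

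- Same r for both formats: 0.
- Interviewer r = 0.9, self r = 0.8: 0.844 − 0.820 = 0.024, about 2 points.
- Interviewer r = 1, self r = 0.8, 0.5 or 0: 0.900 − 0.820, 0.773 or 0.720, that is 8, 12.7 or 18 points.

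Every measured value is at or above the true 0.72. The deficit arises because the format that agrees more closely with the reference is flattered more.

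**If the tablet truly elicits more** (90% against 80%), the true difference is 0.9 × (0.90 − 0.80) = +9 points for self.

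- Interviewer r = 1: self measures 0.810, 0.845 or 0.877 at r = 0, 0.5 or 0.8, against 0.900. That is 9 to 2.3 points worse, a reversed sign.
- Interviewer r = 0.9, self r = 0.8: self measures 0.877 against 0.844, or +3.3 points. The sign is right, but the advantage is understated.

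**Second model, as a check on direction.** Let s be true sensitivity, c the probability that the CIDI detects a true case, and ρ the correlation of TAPS-ESP and CIDI results among true cases. Apparent sensitivity = s + ρ√[s(1−s)c(1−c)] / c. With s = 0.80 for both formats and ρ = 0 for self (assumed):

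- c = 0.95, ρ = 0.3: 0.828 against 0.800, 2.8 points.
- c = 0.90, ρ = 0.5: 0.80 + 0.5 × 0.12 / 0.90 = 0.867 against 0.800, 6.7 points.
- c = 0.70, ρ = 0.5: 0.931 against 0.800, 13.1 points.
- Equal ρ for both formats: 0.

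With true specificity 0.95 and 5% prevalence, apparent specificity differs by only about 0.1 to 0.5 point. Both models tilt the same way whenever the interviewer format is more closely tied to the CIDI than the self format is.

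**The case against.** **The claim concerns order only.** The sentence opens with confounding by order, and a charitable reader would take *unbiased* in that sense. This stands in part. However, the sentence goes on to call the comparison of formats unbiased, and the analysis section counts CIDI-referenced accuracy as part of that comparison. The word needs its limit stated.

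**The large figures come from an extreme assumption.** This stands. The 8–18 points require disclosure on the interviewer format and to the CIDI to coincide exactly, while the same person's tablet answers in the same visit are less closely related. Relaxing that to 0.9 against 0.8 leaves about 2 points and no reversal.

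**The CIDI is the accepted standard and was used in the original English-language study.** This also stands. An interviewer-administered CIDI is not an error. Precedent supports the choice of reference but does not make a between-format contrast against it free of mode effects.

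**Much is already planned.** The self-disclosure comparison needs no CIDI, the oral fluid assay is already a check on self-report, and the article nowhere says that it will rank the formats. This limits the point to one secondary contrast.

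Two stronger readings are tempting and not supported. A reader might infer that the CIDI interviewer knows the earlier TAPS-ESP answers. The article does not say who gives the CIDI or what that person has seen, and a condensed article may leave this to the full protocol. A reader might also infer that better tablet disclosure can never raise the self format's measured sensitivity. The first model shows otherwise: with 80% disclosing to the CIDI, raising tablet disclosure from 80% to 90% lifts it from 0.72 to 0.81 at r = 0.

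**Conclusion.** The point holds for the CIDI-referenced comparison of formats on sensitivity, specificity and ROC curves. Random order cannot remove reference error that is correlated with one format's mode, so calling the comparison unbiased without qualification is too strong, and the contrast may favour the interviewer format.

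The direction is conditional on the interviewer format being more closely tied to the CIDI than the tablet is. The size cannot be found from the documents. Under the assumptions of the first model (equal formats, 80% disclosure in each mode), the spurious sensitivity deficit for self-administration is 0 with equal correlation, about 2 points at 0.9 against 0.8, and 8–18 points only if interviewer-format and CIDI disclosure are identical. Whether a truly better tablet would appear worse depends on the same unknowns.

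The self-disclosure comparison, the validation of each format against the CIDI and the sample size are not undermined.

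**What to change.** Three changes, none needing new data:

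1. In *Study procedures and informed consent*, limit the claim. For example: *Randomising the order removes confounding of the format comparison by administration order.*
2. In *Comparisons by administration format, sex, and age*, add that the between-format contrast in sensitivity, specificity and ROC curves uses an interviewer-administered reference, is subject to shared-mode error that may favour the interviewer format, and will not on its own be used to rank the formats.
3. Add a supporting paired analysis. Among participants with a positive oral fluid result for a substance, compare the proportion disclosing that substance in the self format with the proportion in the interviewer format, accounting for randomised order. Use the medication information already collected to handle positives explained by prescribed medicines.

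The cost is two sentences and one extra analysis, which matters with over two thirds of the sample already recruited. The downsides are real. Oral fluid reflects recent use and not SUD, covers only those who consent to the swab, and will give small numbers for rare substances. The added analysis should therefore support the CIDI-based results and not replace them.
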